## Abstract

**Background:**

Low anterior resection syndrome (LARS) is a common functional problem after sphincter-preserving rectal cancer surgery and includes urgency, frequent bowel movements, clustering, and fecal incontinence. Diverting ileostomy may further disrupt the intestinal environment and alter the gut microbiota, potentially worsening bowel dysfunction after ileostomy closure. However, evidence remains limited on whether bowel stimulation with probiotics before ileostomy closure can improve postoperative bowel function and reduce LARS severity.

**Objective:**

This study aims to evaluate the safety, feasibility, and efficacy of probiotic bowel stimulation through the distal limb of a diverting ileostomy before ileostomy closure in patients with rectal cancer.

**Methods:**

This single-center randomized controlled trial will be conducted at Keimyung University Dongsan Medical Center, Republic of Korea. Eligible participants are adults aged 18‐80 years with clinical stage II or III rectal adenocarcinoma who completed neoadjuvant chemoradiotherapy and underwent laparoscopic or robotic low anterior resection with total mesorectal excision and diverting ileostomy, and who are scheduled for elective ileostomy closure. Participants will be randomly assigned in a 1:1 ratio to receive either 250 mL of normal saline with 4 g of Lacidofil or 250 mL of normal saline alone via the distal limb of the ileostomy once daily for 2 weeks before closure. The primary outcome is the LARS score 3 months after ileostomy closure. Secondary outcomes include postoperative complications, bowel recovery, stool habits, laboratory findings, and length of hospital stay. Analyses will primarily follow the intention-to-treat principle.

**Results:**

The study was approved by the Institutional Review Board of Keimyung University Dongsan Medical Center (DSMC-2024-03-016) and registered with the Clinical Research Information Service (KCT0011052). Recruitment is planned to begin in March 2026 and is expected to continue through March 2029. At the time of manuscript submission, the study is in the pre-enrollment stage, with no participants recruited and no data analysis performed. Results are expected to be published in 2029.

**Conclusions:**

This trial will provide prospective evidence on whether probiotic bowel stimulation before ileostomy closure is a safe and effective strategy for improving postoperative bowel function and alleviating LARS in patients undergoing rectal cancer surgery with diverting ileostomy.

## Introduction

Many patients with rectal cancer who underwent sphincter-preserving surgery experience symptoms such as increased stool frequency, fecal incontinence, irregular bowel movements, soiling, tenesmus, and other issues, collectively referred to as low anterior resection syndrome (LARS) [1,2]. LARS has a multifactorial etiology, including surgical injury to the anal sphincter, pelvic nerve damage, and anatomical changes within the pelvis. Risk factors for LARS include the resection level of the rectum, neoadjuvant chemoradiation, the method of anastomosis, use of a protective ileostomy, and the level of vessel ligation [1,3]. Several methods have been developed to alleviate the symptoms of LARS, including dietary modification, medication such as antispasmodics or constipating agents, pelvic floor rehabilitation, neuromodulation, and transanal irrigation. Despite these efforts, a definitive treatment for LARS remains elusive [2,4].

Diverting ileostomies are frequently performed in patients undergoing rectal cancer surgery, particularly in those at high risks of anastomotic leakage, such as those with a history of radiotherapy [5,6]. Diverting ileostomies provide the advantage of protecting the anastomosis and may reduce the severity of complications in the event of an anastomotic leak. However, the creation of a diverting ileostomy disrupts intestinal continuity, leads to mucosal hypotrophy, and alters the intestinal microenvironment, resulting in loss of intestinal peristalsis due to atrophy of intestinal smooth muscle [7]. Ileostomy closure is associated with postoperative morbidity, including ileus, bowel obstruction, wound complications, infectious complications, and anastomotic leakage, which may delay oral intake and prolong hospital stay [8].

Recent studies have demonstrated that the postoperative intestinal environment significantly impacts gut microbiota, leading to alterations in microbial community composition within the gastrointestinal tract [9,10]. Such changes may increase the proportion of harmful microbes, potentially contributing to severe complications [11,12]. Randomized controlled trials involving patients with colorectal cancer have shown that probiotics can adhere to the colon mucosa, thereby regulating gut microbiota and local immunity [13-15]. A recent study revealed that patients with severe LARS exhibited decreased microbial diversity, characterized by a higher Bacteroidaceae enterotype and reduced abundance of lactic acid-producing microorganisms, including *Bifidobacterium* and *Lactobacillus*, compared to those with mild LARS [15]. However, evidence regarding the role of probiotics in modulating gut microbiota after colorectal surgery and their effect on LARS remains limited [16,17]. Furthermore, the available evidence remains insufficient for routine clinical application in patients undergoing ileostomy closure after rectal cancer surgery [11,12,15,18]. Importantly, the current literature is limited by the small number of randomized or pilot trials, heterogeneity in patient populations, probiotic strains and formulations, timing and duration of administration, routes of delivery, and variation in primary endpoints

Therefore, this study aims to evaluate the safety, feasibility, and efficacy of administering probiotics via the distal limb of a diverting ileostomy before ileostomy closure in patients who underwent rectal cancer surgery. We hypothesize that probiotic bowel stimulation will improve the intestinal microenvironment, be well tolerated, and lead to improved postoperative bowel function, including a reduction in low anterior resection syndrome severity after ileostomy closure.

## Methods

### Study Design

The present study is designed as a single-center, randomized controlled clinical study conducted at Keimyung University Dongsan Medical Center, a tertiary referral hospital in Daegu, Republic of Korea. The study investigates the efficacy and safety of bowel stimulation with probiotics before ileostomy closure in patients with rectal cancer who received preoperative chemoradiation and underwent low anterior resection with ileostomy creation, compared to patients who did not receive probiotics. The protocol has been developed in accordance with the Standard Protocol Items: Recommendations for Interventional Trials (SPIRIT) checklist [19].

### Study Participants

Patients with rectal cancer who have undergone low anterior resection and a diverting ileostomy following chemoradiation and are scheduled for ileostomy closure will be enrolled. The investigator will provide detailed information about the study’s objectives, interventions, potential benefits, risks, and participant rights, allowing sufficient time for consideration. Patients will receive an informed consent form and may voluntarily sign it. Consent will also be obtained for reviewing medical records and collecting blood samples for recurrence assessment. Declining participation will not affect treatment, and patients may withdraw from the study at any time.

Inclusion criteria were as follows: (1) age 18‐80 years; (2) histologically confirmed rectal adenocarcinoma; (3) clinical stage II or III disease; (4) completion of neoadjuvant chemoradiotherapy; (5) prior laparoscopic or robotic low anterior resection with total mesorectal excision and creation of a diverting ileostomy; and (6) planned elective ileostomy closure after confirmation of anastomotic integrity.

Exclusion criteria were as follows: (1) suspected or confirmed inflammatory bowel disease; (2) evidence of anastomotic leakage, stricture, or distal obstruction precluding ileostomy closure; (3) medical contraindication to surgery; (4) severe immune-compromised status or uncontrolled systemic illness; and (5) inability or unwillingness to provide informed consent.

### Randomization and Allocation

Participants will be randomly assigned to either study group in a 1:1 ratio using a computer-generated allocation sequence. To ensure allocation concealment, the sequence will be secured in sequentially numbered, opaque envelopes, open only after participant enrollment. These envelopes will be prepared by a study staff member independent of patient enrollment and data collection. To reduce bias, surgeons performing the operations will remain blinded to group assignment until after anesthesia is initiated.

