### Surgical Techniques and Surgeons

Three experienced surgeons, each having performed over 50 ileostomy closure procedures, will conduct the surgeries. All patients will consume two 200 mL cans of a complex carbohydrate drink 2 hours before surgery and fast thereafter, receiving a second-generation cephalosporin as prophylactic antibiotic therapy. Ileostomy closure will be performed as follows:

Position the patient in a supine position under general anesthesia.Apply aseptic surgical drapes using alcoholic chlorhexidine and povidone-iodine solutions.Make a circular incision around the ileostomy, dissecting in layers until the ileostomy is released from the aponeurosis.Perform ileostomy closure with a side-to-side anastomosis using linear staplers.Ensure hemostasis and close the wound layer by layer.

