### Postoperative Management and Follow-Up

Oral intake will begin the day after ileostomy closure unless obstructive symptoms are reported. Hospital discharge will be determined by the surgeon based on adequate pain control without the need for intravenous or intramuscular analgesics, tolerance of a soft diet, independent ambulation, and absence of significant complications or other medical concerns. Patients will be followed for at least 3 months post-surgery, with visits at 1 week and 1 month. At each visit, patients will be assessed and questioned regarding food acceptance via patient-reported dietary intake logs, stool habits using the Bristol Stool Chart and daily frequency records, and laboratory tests. Three months post-surgery, patients will complete the LARS questionnaire in an outpatient setting. The detailed schedule of assessments is presented in Figure 1.

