### Outcomes

The primary outcome is the LARS score at 3 months after ileostomy closure. The LARS score is a validated patient-reported outcome measure based on 5 items: incontinence for flatus, incontinence for liquid stools, bowel frequency, clustering of stools, and urgency. The total score ranges from 0 to 42, with higher scores indicating more severe bowel dysfunction. Scores are categorized as no LARS (0‐20), minor LARS (21-29), and major LARS (30-42). The questionnaire will be administered in the outpatient clinic at 3 months postoperatively.

The secondary outcomes include (1) postoperative complications within 30 days after ileostomy closure, including ileus, surgical site infection, anastomotic-related complications, readmission, and reoperation; (2) severity of postoperative complications, graded according to the Clavien-Dindo classification; (3) bowel recovery parameters, including time to first flatus, time to first stool passage, and tolerance of oral intake; (4) stool habits, including stool frequency and stool form assessed using patient records and the Bristol Stool Chart; (5) laboratory findings obtained during follow-up; and (6) length of postoperative hospital stay.

Patients will enter an open follow-up phase for up to 5 years for routine postoperative surveillance, monitoring oncologic outcomes and late complications through periodic clinical visits and imaging studies per institutional guidelines.

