### Statistical Analysis

Results will be presented as means with standard deviations for continuous variables and as frequencies and percentages for categorical variables. The *χ*^2^ test or Fisher exact test will be used for categorical data, while the Student’s t-test or Mann-Whitney *U* test will be applied to continuous data. Logistic regression will be conducted for univariate and multivariate analyses. For adjusted analyses, prespecified covariates will include age, sex, body mass index, tumor location, clinical stage, neoadjuvant treatment history, operative approach, anastomotic level, and the interval between index rectal surgery and ileostomy closure. Exploratory subgroup analyses may be performed according to sex, age group, operative approach, and anastomotic level. Because the study is not powered for subgroup comparisons, these analyses will be interpreted cautiously. A *P* value <.05 will be considered statistically significant.

Analyses will be conducted on an intention-to-treat basis, including all randomized participants in their assigned groups, regardless of protocol adherence. A per-protocol analysis will be performed as a sensitivity analysis to assess result robustness. For missing data, multiple imputation methods will be employed, assuming data are missing at random. Sensitivity analyses will evaluate the impact of missing data on primary and secondary outcomes. Statistical analyses will be conducted using SPSS software (version 25; IBM Corp., Armonk, NY, USA).

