## Results

### Study Status and Timeline

The study protocol received approval from the Institutional Review Board of Keimyung University Dongsan Medical Center (IRB No. DSMC-2024-03-016) and was registered with the Clinical Research Information Service, Republic of Korea (KCT0011052). Participant recruitment is scheduled to begin in March 2026 and is expected to continue through March 2029. The target sample size is 100 participants, with 50 participants allocated to each study group. Final data collection for the primary endpoint will be completed after the 3-month follow-up of the last enrolled participant, and the main study findings are expected to be published in 2029.

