Despite these strengths, the study has several limitations that warrant consideration. First, as a single-center trial, the results may not be fully generalized to populations with differing demographic characteristics, clinical settings, or surgical practices. To address this limitation, the trial employs clearly defined eligibility criteria, standardized surgical techniques performed by experienced surgeons, and rigorous data collection protocols to enhance reproducibility. Future multi-center trials with larger and more diverse populations will be essential to confirm external validity. Second, the intervention uses a single probiotic formulation (Lacidofil), which may limit the applicability of findings to other probiotic strains or combinations, as their efficacy and microbial interactions may vary. While this choice ensures consistency and minimizes confounding from strain heterogeneity, subsequent research could explore alternative formulations, dosages, or delivery regimens to optimize outcomes. Third, although all participating surgeons have substantial experience with ileostomy closure (>50 cases each), subtle variations in operative technique and postoperative care, as well as variability in patient adherence to postoperative protocols (eg, dietary intake logs and follow-up visits), could introduce minor biases. To reduce these effects, the study employs standardized perioperative protocols, surgeon blinding until anesthesia induction, and adherence monitoring through patient diaries and scheduled follow-ups. Finally, the follow-up period specified for the primary endpoint (3 mo) may not capture long-term effects of the intervention on bowel function and oncologic outcomes. However, an open follow-up phase of up to 5 years is incorporated to collect extended outcome data, and future studies with even longer observation and mechanistic analyses, such as microbiome profiling and immune modulation assessments, will be important to fully elucidate the sustained impact of probiotic administration.

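### Operating surgeon is missing from the prespecified covariates, although three surgeons operate and decide discharge and the article names variation in technique and care as a possible source of minor bias

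*Protocol article*

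**What the plan says.** - **Who operates.** Surgical Techniques and Surgeons: "Three experienced surgeons, each having performed over 50 ileostomy closure procedures, will conduct the surgeries".
- **Who decides discharge.** Postoperative Management and Follow-Up: "Hospital discharge will be determined by the surgeon based on adequate pain control". Further criteria follow: diet, ambulation, and absence of significant complications. Outcomes lists "length of postoperative hospital stay" as the sixth secondary outcome, so the operator has a hand in an endpoint.
- **Allocation.** Randomization and Allocation: "Participants will be randomly assigned to either study group in a 1:1 ratio using a computer-generated allocation sequence". Neither blocks nor strata are mentioned. The same section says that "surgeons performing the operations will remain blinded to group assignment until after anesthesia is initiated".
- **Adjustment.** Statistical Analysis: "prespecified covariates will include age, sex, body mass index, tumor location, clinical stage, neoadjuvant treatment history, operative approach, anastomotic level". The ninth and last covariate is the time from rectal surgery to closure. Surgeon is not on the list.
- **The acknowledged source of variation.** The limitations in the Discussion name "subtle variations in operative technique and postoperative care" as something that could introduce minor biases, despite the surgeons' experience. The countermeasures given are standardized perioperative protocols, surgeon blinding up to induction, and adherence monitoring.

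**The concern.** The article identifies variation between operators, but its countermeasures do not deal with operator as a factor. Standardization may shrink the differences, and diaries track patient adherence. Blinding stops once anesthesia has begun, before the operation and the discharge decision. None of these evens out surgeons between arms or takes their differences out of the comparison. The covariate list could do the latter, and it is stated explicitly, so the omission is a choice on the page rather than a detail left to another document.

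At stake is precision and, in any one realized trial, an uneven spread of operators by chance. If one surgeon tends to discharge earlier and happens to have more patients in one arm, the unadjusted difference in length of stay moves with that imbalance. Bowel recovery and complications are exposed in the same way.

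**Working it through.** **Inputs from the article.** Three surgeons. Target difference 3 LARS points, SD 5, two-sided alpha 0.05, power 80%, 45 per group, 10% dropout, 50 per group. **Assumed, because the article gives no figures:** surgeon caseloads and the size of surgeon effects.

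**1. The stated sample size.** The normal approximation gives n = 2(1.96 + 0.84)² × 5²/3² = 43.6, so 44 per group. The two-sample t-test gives 44.6, so 45. With dropout, 45/(1 - 0.10) = 50. The stated figures reproduce, and nothing below changes them.

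**2. How uneven the surgeons' shares can be.** For a surgeon with one third of the cases and 50 patients per arm, the SD of the between-arm difference in share is √[(1/3)(2/3)(1/50 + 1/50)] = √0.00889 = 0.094, about 9.4 percentage points. Simulation of 50:50 allocation not stratified by surgeon gives the chance that at least one surgeon's share differs by the stated amount:

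| Assumed caseloads | 10 points or more | 20 points or more |
|---|---|---|
| 34/33/33 | 63% | 11% |
| 50/30/20 | 50% | 12% |
| 60/25/15 | 55% | 8% |

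Ten points is roughly one SD for a single surgeon, so a high chance for the largest of three is expected and is not alarming in itself. These figures apply only if the full protocol does not stratify by surgeon.

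**3. What the imbalance does to the estimate.** With equal caseloads, the SD of the chance shift in the arm difference is √[V(1/50 + 1/50)] = √(0.04V), where V is the variance of the surgeon effects.

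- LARS effects of -1.5, 0, +1.5: V = (2.25 + 0 + 2.25)/3 = 1.5. SD = √0.06 = 0.245. The 95% limit is 1.96 × 0.245 = 0.48 points.
- LARS effects of -3, 0, +3: V = 6. SD = √0.24 = 0.49. The 95% limit is 0.96 points.
- Length of stay, effects of -0.5, 0, +0.5 days: V = 0.167. SD = √0.00667 = 0.082. The 95% limit is 0.16 days.

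As a single worked case, a 20-point imbalance between two surgeons who differ by 3 points shifts the difference by 0.20 × 3 = 0.6 points.

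**4. Type I error and power.** Simulation with 90 evaluable patients, equal caseloads, total SD 5 and a 3-point effect:

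| Surgeon effects | Type I error, unadjusted / adjusted | Power, unadjusted / adjusted |
|---|---|---|
| 0, 0, 0 | 4.7% / 4.6% | 81% / 80% |
| -1.5, 0, +1.5 | 4.9% / 4.7% | 81% / 82% |
| -3, 0, +3 | 4.8% / 4.8% | 80% / 89% |

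The gain comes from removing V from the residual variance, for example 25 - 6 = 19 (SD 4.36) in the last row. That row assumes a 6-point range between surgeons, wider than the assumed SD of 5.

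**The case against.** The strongest case against the point is that nothing here is stated wrongly. Random allocation balances surgeons in expectation, and the standard error already allows for chance imbalance. The article calls the biases minor, fixes one stapled side-to-side technique for all three surgeons, and gives several discharge criteria. The primary outcome is patient-reported at 3 months. The Introduction attributes LARS to matters such as resection level, radiation and anastomotic method, not to who closes the stoma, and several of these are already covariates. Unstratified allocation in a single-center trial with three surgeons is acceptable practice. All of this stands and limits the weight of the point. It does not explain why surgeon is missing from an explicit adjustment list when the article names operator variation as a limitation.

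A reader might infer three stronger things that the article does not support.

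- **That randomization is a plain sequence without blocks or strata.** The section is silent on restriction, which an article commonly leaves to the full protocol. Silence is not a statement that allocation is unrestricted.
- **That 50 per group will not be delivered.** "The target sample size is 100 participants, with 50 participants allocated to each study group" is a target and is compatible with blocking. Missing it slightly would also cost little: with 90 evaluable patients, power is 80.4% at 50:50, 80.0% at 55:45 and 78.8% at 60:40.
- **That no analysis could separate surgeon from product.** A model with surgeon as a factor does so, provided that each surgeon treats patients in both arms.

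**Conclusion.** The point holds as a modest improvement to a stated list. The article names operator variation, yet its countermeasures neither balance nor adjust for surgeon, and the prespecified covariates omit it. Type I error stays near 5% and there is no systematic bias. What is left is chance imbalance by operator and some lost precision, which matter most for length of stay and bowel recovery.

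Little effect is expected on the 3-month LARS score: a chance shift of about 0.5 points at the 95% limit under moderate surgeon effects, and about one point of power gained by adjusting. The gain reaches about 9 points only under the extreme assumption of a 6-point range. These sizes rest on assumed caseloads and surgeon effects.

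**What to change.** Before recruitment starts:

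1. Add operating surgeon at ileostomy closure, as a three-level factor, to the prespecified covariates in Statistical Analysis.
2. Use it in the adjusted analyses of length of stay and bowel recovery, and in that of the LARS score for consistency.
3. Report the number of patients per surgeon in each arm.

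**Cost.** Two degrees of freedom, and about one point of power if surgeons do not differ (81% to 80% in the simulation). The sample size is unchanged. The article reports that no one has yet been randomized, so the list can still be changed before any data exist.

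**Optional addition.** If the full protocol does not already restrict randomization, and the operating surgeon is known at enrollment (the article does not say), allocation could be stratified by surgeon in concealed blocks of varying size. The price is more envelope handling and some predictability: surgeons are unblinded after anesthesia starts and would learn past allocations in their own series. Varying block sizes reduce this risk but do not remove it. Adjustment alone is enough to resolve the point.

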### Probiotics Administration

The patients will receive a 14-French Foley catheter, normal saline, and probiotics (Lacidofil®) containing *Lactobacillus rhamnosus* R0011 and *Lactobacillus acidophilus* R0052 bacterial culture (2×109 colony-forming units) in an outpatient setting. This formulation was considered appropriate for the present trial because Lactobacillus-based probiotics have been investigated in colorectal and other gastrointestinal settings as microbiota-modulating interventions, although evidence remains inconclusive regarding their effect on postoperative bowel function and LARS [20]. The probiotic dose was selected to ensure a practical and standardized daily regimen for outpatient administration while remaining aligned with the commercially available formulation and with doses that have been evaluated in prior studies using the same product or closely related probiotic preparations [21]. The intervention group will receive 250 mL of normal saline with 4 g of Lacidofil® administered via the distal limb of the ileostomy once daily for 2 weeks prior to ileostomy closure. The control group will receive 250 mL of normal saline without probiotics using the same method. The 250 mL of normal saline will be infused over 10‐15 minutes via a 14-French Foley catheter with the patient in a supine position. Adherence will be monitored through daily patient diaries and weekly outpatient visits. Patients will record abdominal symptoms, including pain, nausea, vomiting, diarrhea, and gas and stool passage during the 2-week period before ileostomy closure.

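### The surgeon blind is set to end once anesthesia starts, before every listed outcome and with no stated reason, which leaves surgeon-decided discharge, and so length of stay, open to bias

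*Protocol article*

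**What the plan says.** Randomization and Allocation gives the only blinding measure in the article, and gives the time at which it stops: "surgeons performing the operations will remain blinded to group assignment until after anesthesia is initiated". The same section has the allocation envelopes prepared by a staff member who takes no part in enrolment or data collection.

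Probiotics Administration has the study product "administered via the distal limb of the ileostomy once daily for 2 weeks prior to ileostomy closure". For the comparator, "The control group will receive 250 mL of normal saline without probiotics using the same method".

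Surgical Techniques and Surgeons describes one closure procedure for all patients, including the step "Perform ileostomy closure with a side-to-side anastomosis using linear staplers".

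Postoperative Management and Follow-Up states: "Hospital discharge will be determined by the surgeon based on adequate pain control", followed by further criteria on diet, walking and absence of complications. Outcomes lists "length of postoperative hospital stay" as the sixth secondary outcome.

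The limitations part of the Discussion acknowledges possible bias from variation in operative technique, postoperative care and patient adherence. Among the measures meant to reduce it, it names "surgeon blinding until anesthesia induction, and adherence monitoring through patient diaries and scheduled follow-ups".

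**The concern.** A blind that ends at anesthesia suits a trial in which the randomized treatment is the operation itself, because the surgeon must then learn the arm. Here the randomized treatment has finished, and no described surgical step depends on the arm. The rule therefore protects the surgeon's judgement up to the point at which the listed outcomes begin to form, and then stops.

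What is at stake is mainly length of stay. The person who decides discharge may know the arm, and some of the criteria (adequate pain control, no significant complications, no other medical concerns) call for judgement. A shift in discharge timing caused by knowledge of the arm cannot be told apart from a treatment effect at analysis, and no later adjustment removes it.

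This is a rule that the article states, not a detail left to a fuller document. No participants had been randomized at submission, so it can still be changed before it does harm.

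**Working it through.** **1. Order of events.** Set side by side, the sections give this sequence:

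| Step | Section | Operating surgeon blinded? |
|---|---|---|
| Infusion for 2 weeks, with symptom and adherence diaries | Probiotics Administration | Yes |
| Anesthesia initiated | Randomization and Allocation | Blind ends |
| Closure, one technique for all | Surgical Techniques and Surgeons | Not protected |
| Bowel recovery, discharge, length of stay | Postoperative Management; Outcomes | Not protected |
| 30-day complications and their grading | Outcomes | Not protected |
| Stool habits, laboratory findings in follow-up | Outcomes | Not protected |
| LARS score at 3 months | Outcomes | Not protected |

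All seven outcomes listed (one primary, six secondary) fall after the blind ends. The pre-closure diaries fall before it. They bear on the safety and feasibility aims but are not on the outcome list.

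**2. Need for unblinding.** The infusion is complete, the operative steps do not differ by arm, and the text gives no reason for telling the surgeon.

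**3. Which outcomes the surgeon can influence, on the text.**
- Length of stay: directly, because the surgeon determines discharge.
- Complications, their grade, tolerance of intake: possibly. The assessor is not named.
- First flatus and first stool: these rest largely on what the patient reports.
- LARS score: a patient questionnaire, so only indirectly.

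**4. The Discussion's safeguard.** Technique and postoperative care both come after induction. A blind that has already ended can do little about either.

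**5. The plan's own figure.** The sample size reproduces. With a difference of 3 and an SD of 5, d = 3/5 = 0.6. A two-sided t-test at .05 with 80% power needs 44.6, rounded up to 45 per group, and 45/0.90 = 50 per group. Longer blinding does not change this.

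**6. Illustration for length of stay.** The article gives no length-of-stay SD, so the SD and the size of the shift are assumptions. Suppose no true effect, 50 per arm, a two-sided t-test at .05, and every patient in one arm discharged s days earlier because the arm is known. Then d = s/SD and the noncentrality is d × √(50/2) = 5d, with 98 degrees of freedom and critical value 1.984.

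| SD (days) | s = 0.5: d, 5d, P<.05 in | s = 1: d, 5d, P<.05 in |
|---|---|---|
| 2 | 0.250, 1.25, 23.6% | 0.500, 2.50, 69.7% |
| 3 | 0.167, 0.83, 13.1% | 0.333, 1.67, 37.9% |
| 4 | 0.125, 0.63, 9.5% | 0.250, 1.25, 23.6% |

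The nominal rate is 5%. The Mann-Whitney test, which the plan also allows, would give somewhat different figures.

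**The case against.** Several stronger readings are tempting, and the document does not support them.

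- **That complications and bowel recovery are in fact assessed with knowledge of the arm.** The article does not say who diagnoses ileus, grades complications or records flatus, stool and intake, and the blinding sentence concerns operating surgeons only. The full protocol, which the article says will be public through the registry, may name blinded assessors. Only *may be* is supported.
- **That the primary result is directly biased.** LARS is completed by the patient. The surgeon's knowledge could reach it through care or conversation, but that route is indirect.
- **That no data at all precede unblinding.** The tolerability and adherence diaries do.
- **That the Discussion credits blinding alone with controlling postoperative care.** It names three measures together against a group of effects. The fair criticism is that this one adds little for technique and aftercare.
- **That the percentages describe this trial.** They show what a uniform bias of an assumed size would do. They are not evidence that such a bias will occur.

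It can also be said that the discharge criteria limit discretion. They do, particularly the requirement that no injected analgesics be needed, but they do not remove it.

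A further objection concerns the remedy. One arm mixes a product into saline and the other uses saline alone, and no masked product or participant blinding is described. Participants may know their arm and tell the surgeon. This stands: a longer blind may be imperfect and is not entirely free. It is not a reason to end the blind on purpose.

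**Conclusion.** The point holds in a limited form. The article ends the operating surgeons' blind at the start of anesthesia, before every listed outcome and without a stated or apparent need. The exposure that the text clearly supports is one secondary outcome, length of stay, through surgeon-determined discharge. Exposure of complications and bowel recovery is possible but not established, and exposure of the LARS score is indirect. The Discussion's reliance on "surgeon blinding until anesthesia induction" as a safeguard for technique and postoperative care is misplaced, because both come later.

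Under the assumptions stated (SD 2 to 4 days, uniform shift, t-test, 50 per arm), false-positive rates for length of stay would be about 9% to 24% for a half-day shift and about 24% to 70% for one day. No documented figure fixes where in that range, if anywhere, this trial would lie. It should be fixed as a cheap improvement. It does not undermine the primary analysis.

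**What to change.** In Randomization and Allocation, delete the clause that ends the surgeons' blind at anesthesia. State instead that operating surgeons and, where feasible, those who decide discharge or grade complications stay blinded through the 3-month LARS assessment, except for documented emergency unblinding. Let the independent staff member who prepares the envelopes hold the code. Amend the limitations part of the Discussion so that it describes the blind as it will then operate.

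Ask participants not to disclose their arm to surgeons or assessors, and report the blind as possibly imperfect, since no masked product is described.

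For the surgeons, the cost is a change of wording and one unblinding step fewer, with no extra staff and no change in sample size. The remaining costs are the instruction to participants and any arrangement for blinded discharge decisions or grading.
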